### Study oversight and organisation

The core team of the MERCURI-2 investigator group consists of three principal investigators from the Amsterdam UMC and the trial coordinator. This team is responsible for the design of the study protocol and progress of the trial. The core team will draft the final report that will be approved by all MERCURI-2 investigators. The trial is conducted under supervision of an independent Data and Safety Monitoring Board (DSMB), consisting of two clinical experts and an epidemiologist. An independent statistician will present unblinded data to the DSMB. The DSMB reviews the incidence of AKI in the placebo group after 25% of the participants have been included, in order to inform the sample size calculation. The DSMB reviews the incidence of AKI at two predefined intervals (after inclusion of 25% and 50% of participants) to assess safety outcomes including AKI. No specific stop criteria were determined.

The study will be monitored by the Clinical Research Unit from the Amsterdam UMC. Each involved study site will receive a baseline and close-out visit and additional visits after the inclusion of 10 and 100 participants during the study. The monitor will approve informed consent papers, verify the serious adverse events (SAEs) and check data collection and quality of registration.

Regarding SAEs, the sponsor will yearly present an overview of the SAEs via Clinical Trials Information System (CTIS). SUSARs will be reported earlier via EudraVigilance depending on the seriousness of the reaction and will be as follows: in the case of fatal or life-threatening SUSARs, as soon as possible and in any event not later than 7 days after the sponsor became aware of the reaction; in the case of non-fatal or non-life-threatening SUSARs, not later than 15 days after the sponsor became aware of the reaction and in the case of SUSARs which were initially considered to be non-fatal or non-life-threatening but which turn out to be fatal or life-threatening. as soon as possible and in any event not later than 7 days after the sponsor became aware of the reaction being fatal or life-threatening.

### Sample size calculation

Sample size is based on Fisher’s exact test, with an expected AKI incidence in the placebo group of 22%, based on previous cohorts,^2^ taking a conservative estimation. A relative risk of 0.64 based on AKI reduction by SGLT2 inhibitors in previous trials^6^ translates into an absolute risk reduction of 7.9% and incidence in the intervention group of 14.1%. The required total sample size to find such a difference with two-sided alpha of 0.05 and 80% power is 784. We therefore aim to include 392 patients per arm.

### Achieve sample size

Based on previous trials and the short trial duration per patient, we expect a low number of drop-outs. If a drop-out occurs, for example due to surgery cancellation or withdrawal of informed consent, dropouts will be replaced to maintain sufficient statistical power.

#### Statistical analyses

The baseline characteristics of all subjects, per treatment group, will be outlined in a table describing variables such as demographic variables, weight, length, relevant medical history and current medication use. Continuous data will be presented as mean with SD or as median with IQR, depending on the distribution of the data. Distribution of data will be assessed with histograms, Q-Q plots and the Shapiro-Wilk test. We expect a small percentage of missing data due to the in-hospital setting and short duration of the study.

### Primary study outcome

Statistical analyses will be based on an intention-to-treat approach. The main analysis will concern the comparison of the incidence of AKI between both groups. The disparity in AKI incidence will be evaluated using the Fisher’s exact test. In addition, the risk difference of AKI between both groups, along with the associated 95% CIs, will be presented.

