**Methods and analysis:**

We designed a multicentre, randomised, placebo-controlled, triple-blinded, superiority trial. A total of 784 patients, aged above 18 years, undergoing cardiac surgery will be included with stratification for sex and type 2 diabetes in a 1:1 ratio. Patients will receive either dapagliflozin 10 mg or placebo from the day before until 2 days after surgery. Serum creatinine will be measured preoperatively and daily for the first 7 days after the operation, and urine output will be measured until the urinary catheter is removed. The primary outcome is the incidence of postoperative AKI according to the KDIGO criteria.

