### Randomisation

After inclusion, patients will be randomised by Castor EDC. Block randomisation with computer-generated blocks of 4, 6 or 8 patients will be used. The block size will be unknown to the researchers. Randomisation is stratified for sex, presence of T2D and study site.

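### The primary AKI comparison is an unadjusted Fisher's exact test that uses neither the randomisation strata nor the recorded baseline creatinine; the test is valid and meets its stated power, but it gives up a modest amount of efficiency

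*Protocol article*

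**What the plan says.** All references are to the protocol article.

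- **Randomisation:** "Randomisation is stratified for sex, presence of T2D and study site". The same section adds: "Block randomisation with computer-generated blocks of 4, 6 or 8 patients will be used".
- **Primary study outcome:** "The disparity in AKI incidence will be evaluated using the Fisher’s exact test". The effect measure follows: "In addition, the risk difference of AKI between both groups, along with the associated 95% CIs, will be presented". Neither sentence mentions a stratum or a covariate.
- **Sample size calculation:** the trial is sized on the same test, "Sample size is based on Fisher’s exact test, with an expected AKI incidence in the placebo group of 22"%. A relative risk of 0.64 gives 14.1% under dapagliflozin. The result is 784 patients, 392 per arm, at two-sided 5% and 80% power.
- **Secondary study outcomes:** sex and type 2 diabetes enter interaction models only. Baseline kidney function enters only a regression of effect modification. Site enters no analysis.
- **Study design:** the most recent preoperative creatinine is recorded. The KDIGO creatinine criteria in Table 2 need a baseline value in any case.

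**The concern.** Stratified blocks force the arms to be nearly balanced on sex, diabetes and site. If those factors predict AKI, the variation between strata largely drops out of the true sampling variance of the difference in AKI rates. An unadjusted test still charges for it. The rejection rate under no effect then falls below 5%, and an interval computed without the strata is wider than it needs to be. The design works to balance these factors and the analysis does not collect the benefit.

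Two further sources of efficiency are left unused. Fisher's test is conservative in its own right because the table counts are discrete. Baseline creatinine, if it is prognostic, could sharpen the comparison at no cost in data collection.

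At stake is some power on the trial's only primary question, in a plan that aims at exactly 80%.

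**Working it through.** **Step 1. Reproduce the plan's figure.** Inputs from Sample size calculation: control rate 0.22, treated rate 0.141 (0.22 × 0.64 = 0.1408), 392 per arm, two-sided 5%. Exact power sums the binomial probabilities of all 2×2 tables in which the two-sided Fisher p-value is at most 0.05.

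| Per arm | Fisher power |
|---|---|
| 390 | 79.8% |
| 392 | 80.0% |
| 394 | 80.1% |

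The stated 784 reproduces.

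**Step 2. Conservatism of Fisher's test by itself.** The same enumeration under a common rate, at 392/392:

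- Fisher: true size 4.06% at 18.05% (the mean of the two planned rates) and 4.10% at 22%; power 80.0%.
- Pearson chi-square, uncorrected: size 5.0%, power 82.4%.

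The gap is largest when the arms are exactly equal. At 391/393 Fisher has size 4.5% and power 81.5%; at 390/394, 4.5% and 80.7%. So Fisher's simulated power in Step 3, where the arms are rarely exactly equal, lies a little above 80.0%. Gains must therefore be measured against Fisher within the same simulation.

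**Step 3. Adding the strata and baseline kidney function.** The setting was N = 784, permuted blocks of 4, 6 or 8 within sex × diabetes × site, marginal rates held at 22% and 14.1%, and 8,000 runs per scenario (Monte Carlo standard error about √(0.82 × 0.18 / 8000) = 0.4 points for power). Assumptions **not** in the documents are 5 sites, 25% women, 25% with type 2 diabetes, and the prognostic strengths shown. CMH is the Cochran–Mantel–Haenszel test on the strata. Logistic is the Wald test of treatment with sex, diabetes, site and baseline kidney function in the model.

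| Assumed prognostic strength | Fisher | Pearson | CMH | Logistic | Logistic − Fisher |
|---|---|---|---|---|---|
| (a) none | 80.7 | 82.1 | 82.0 | 82.0 | 1.3 |
| (b) weak strata (log-odds 0.2 sex, 0.3 diabetes, small site spread) | 81.4 | 82.8 | 82.9 | 83.0 | 1.7 |
| (c) moderate strata (0.4, 0.5, wider site spread) | 81.9 | 83.3 | 84.5 | 84.6 | 2.6 |
| (d) weak strata, kidney function OR 1.5 per SD | 81.4 | 82.9 | 83.3 | 84.3 | 3.0 |
| (e) moderate strata, kidney function OR 2 per SD | 82.4 | 83.9 | 84.9 | 87.1 | 4.7 |

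(Power in %; differences taken before rounding.)

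Splitting the gain:

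- Fisher to Pearson: 1.4–1.5 points in every scenario. This is discreteness and has nothing to do with the strata.
- Pearson to CMH: −0.1, 0.1, 1.2, 0.4 and 0.9 points for (a) to (e). This is the part due to the strata.
- CMH to logistic: about 0 in (a) to (c), 1.1 in (d), 2.3 in (e). This is the part due to baseline kidney function.

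Size under no effect was 3.9–4.8% for Fisher and 4.9–5.5% for CMH and logistic (standard error about 0.24 points). In (c), Pearson fell to 4.3% while CMH was 4.9%, which shows the extra conservatism from ignoring prognostic strata.

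**Step 4. Translation into patients.** A second simulation tested the standardised risk difference. It assumed 6 sites and a log-odds ratio of 0.4–0.8 per SD of kidney function, with 1,500 runs per scenario (standard error about 1 point). The equivalent sample-size ratio is [(z_adj + 1.96) / (z_Fisher + 1.96)]², where z is the normal quantile of the power.

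| Adjusted | Fisher, same runs | Ratio |
|---|---|---|
| 82.9% | 80.5% | (2.910 / 2.820)² = 1.065 |
| 85.5% | 81.3% | (3.018 / 2.849)² = 1.122 |
| 86.7% | 81.7% | (3.072 / 2.864)² = 1.151 |

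This is worth roughly 6.5–15% more patients. Using the exact 80.0% as comparator would give 1.08 and 1.20 at the two ends, but that sets a simulated figure against one that holds only for exactly equal arms.

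**The case against.** The strongest reply is that nothing promised is lost. The trial is sized for the test it will use, 392 per arm delivers the stated 80%, type I error stays below 5%, and the risk difference is interpretable. That stands. A reader might infer from the stratification mismatch that the test is invalid or the trial underpowered; the documents support neither. Whether the assumed effect is realistic is a separate question.

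Second, little of the gain comes from the strata, and the larger gains need prognostic strengths that the documents do not give. That also stands. Baseline kidney function is not a stratification factor, and baseline creatinine is itself part of the KDIGO ratio, so its prognostic value cannot be taken for granted. Adjusting for it is an efficiency recommendation; ignoring the strata is the firmer criticism.

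Third, two nearby readings are tempting and should not be pressed:

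- The abstract names only sex and diabetes ("undergoing cardiac surgery will be included with stratification for sex and type 2 diabetes in a 1:1 ratio"). It does not say that these are the only factors, and the Randomisation section gives the full list. This is condensation.
- The Fisher p-value and the risk-difference interval might disagree near 5%. The article does not name the interval method, and that detail is commonly left to the full protocol or SAP.

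Fourth, the change is not free: recruitment began in June 2023 and an amendment needs ethics approval. That is a real but small cost. What does not stand is the idea that the choice of test is merely left to an unseen SAP, because the article names the primary test and sizes the trial on it.

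**Conclusion.** The point holds as a worthwhile improvement, not as the correction of an error. The planned test is valid and has its stated power, but it is conservative (true size about 4.1% with equal arms) and uses neither the strata nor baseline creatinine. At the same 784 patients an adjusted analysis would have about 82–87% power, a gain over Fisher of about 1–5 points like for like. About 1–2 points come from replacing Fisher; the rest comes from the strata and baseline kidney function.

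The Fisher and Pearson figures are exact under the plan's own rates. The remainder depends on assumed site numbers, sex and diabetes shares and prognostic strengths. In the scenario with nothing prognostic, adjustment cost no more than about 0.1 points against Pearson and still beat Fisher.

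**What to change.** Before database lock and unblinding, amend Primary study outcome so that:

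- the primary analysis is a logistic regression on treatment, sex, type 2 diabetes, site and baseline creatinine or eGFR (choose one);
- small sites are pooled by a rule fixed in advance, since sex × diabetes × site cells may be sparse;
- the result is the standardised (marginal) risk difference with its 95% CI and the p-value from the same procedure;
- the unadjusted Fisher's exact test is kept as a sensitivity analysis.

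The sample size can stay as it is. No new data are needed: the strata are known at randomisation and preoperative creatinine is already recorded. The cost is a protocol amendment through the ethics committee and agreement on the pooling rule. The article keeps investigators blinded until database lock, so the change can still be made without knowledge of results by arm, provided that those who draft it have not seen the unblinded data presented to the DSMB.

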### Secondary study outcomes

Heterogeneity of treatment effect between men and women will be studied for the primary outcome by examining a treatment-by-sex interaction effect in a logistic regression model with treatment and sex as main effects. Similarly, the heterogeneity of treatment effect in patients with and without T2D will be studied using the same approach. Treatment effect estimates, along with their corresponding 95% CIs, will be reported for each specific subgroup. Other secondary outcomes will be presented as number of events and analysed with the Fisher’s exact test. Continuous data will be presented as mean with SD and differences will be assessed employing the Student’s t-test. Generalised mixed-effect models will be constructed to examine potential differences in the repeated measurements. Predefined post hoc analysis with regression analyses will be conducted to estimate the influence of age, BMI, baseline kidney function and the presence of heart failure on the treatment effect and their possible interactions on the primary outcome. A 2-sided p value <0.05 will be considered statistically significant. Statistical uncertainty will be expressed in 2-sided 95% CIs.

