	Urine output	<0.5 mL/kg/h	For >12 hours
3	Start renal replacement therapy		
	Serum creatinine	3.0 times baseline or	Within 7 days
		≥4.0 mg/dL	
	Urine output	<0.3 mL/kg/h or	>24 hours
		Anuria	>12 hours

**Table 3 T3:** Recorded secondary and exploratory outcomes

Outcome measures	Time frame	Definition
Secondary outcomes		
Individual AKI stages	≤ 7 days postoperative	Incidence of stage 1, 2 and 3 AKI according to KDIGO criteria
Creatinine	≤ 7 days postoperative	Postoperative maximum change of creatinine compared with baseline creatinine
AF	≤ 7 days postoperative	Postoperative AF recorded with an ECG or for which treatment is initiated
LoS-ICU	≤ 30 days postoperative	LoS-ICU, measured in days from transfer to ICU until discharge from ICU
LoS-Hos	≤ 30 days postoperative	LoS-Hos, measured in days from surgery until discharge from the hospital
MAKE	≤ 30 days postoperative	MAKE. Composite endpoint of death, new dialysis and worsened renal function
MACE	≤ 30 days postoperative	MACE. Composite endpoint of cardiovascular death, nonfatal myocardial infarction, nonfatal ischaemic cerebral vascular accident and hospitalisation for heart failure
Safety outcomes	≤ 30 days postoperative	Genital mycotic infections, diabetic ketoacidosis and hypoglycaemia
Hypoglycaemia	≤ 3 days postoperative	Incidence of hypoglycaemia (blood glucose <4 mmol/L) detected during routine perioperative glucose measurements
Hyperglycaemia	≤ 3 days postoperative	Incidence of hyperglycaemia (blood glucose >10 mmol/L) detected during routine perioperative glucose measurements
Cardiac biomarker 1: troponin	From transfer to ICU until 48 hours postoperatively	Peak troponin concentration as routinely measured during clinical practice
Cardiac biomarker 2: CK-MB	From transfer to ICU until 48 hours postoperatively	Peak CK-MB concentration as routinely measured during clinical practice
Patient-reported quality of recovery 1	Recorded at 30 days postoperatively	According to Days at Home in first 30 days
Patient-reported quality of recovery 2	Recorded at 30 days postoperatively	According to WHO Disability Assessment Schedule 2.0
Patient-reported quality of recovery 3	Recorded at 30 days postoperatively	According to 5 level EuroQol 5-Dimensions questionnaire
Exploratory outcomes		
Systemic haemodynamics 1	From start of anaesthesia until discharge from the ICU, assessed up to 72 hours	Perioperative hourly average heart rate

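### An unadjusted t-test for every non-repeated continuous secondary outcome is valid but inefficient for creatinine change and biomarker peaks, and the stay and single-stage AKI outcomes can mislead

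*Protocol article*

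**What the plan says.** All references are to the protocol article.

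- **Secondary study outcomes** gives one rule for continuous data: "Continuous data will be presented as mean with SD and differences will be assessed employing the Student’s t-test". It names no alternative for skewed data and no covariate. Repeated measurements go to mixed-effect models. Remaining outcomes are counted as events and compared by Fisher's exact test.
- **Statistical analyses**, directly after a sentence on the baseline table, says: "Continuous data will be presented as mean with SD or as median with IQR, depending on the distribution of the data". Histograms, Q-Q plots and the Shapiro-Wilk test are to judge the distribution.
- **Table 3** lists the outcomes that the t-test rule reaches. They include maximum creatinine change from baseline, ICU stay, hospital stay ("LoS-Hos, measured in days from surgery until discharge from the hospital"), troponin ("Peak troponin concentration as routinely measured during clinical practice") and CK-MB.
- **Table 3** also lists AKI severity as "Incidence of stage 1, 2 and 3 AKI according to KDIGO criteria".

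**The concern.** A single unadjusted comparison of means is applied to outcomes of very different kinds.

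- Maximum creatinine change is defined against a baseline value that the analysis then does not use.
- Peak troponin and CK-MB are maxima of positive quantities and may well be right-skewed, so a few extreme patients can dominate the mean.
- A stay that ends at discharge has no defined end for a patient who dies in hospital. If the day of death is used, an early death counts as a short stay, and harm could look like benefit.
- Single AKI stages are ordered categories. A treatment that moves patients from stage 2 or 3 into stage 1 can raise the stage 1 count while severity falls.

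At stake are the precision and the reading of secondary results, not the primary conclusion.

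**Working it through.** **The plan's own figure.** The Sample size calculation section states: "The required total sample size to find such a difference with two-sided alpha of 0.05 and 80% power is 784", with AKI rates of 22% and 14.1%, and "We therefore aim to include 392 patients per arm". Full enumeration of the two-sided Fisher test at 392 per arm gives 80.0% power, so the figure reproduces. No SD, distribution or power is given for any secondary outcome. The SDs, shapes and correlations below are therefore assumptions.

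**Maximum creatinine change.** Let r be the correlation between baseline and postoperative maximum, with equal variances s² (assumption).
- Variance of the change score: 2s²(1 − r).
- Residual variance under ANCOVA: s²(1 − r²).
- Ratio: 2/(1 + r).

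| assumed r | variance ratio | 392 per arm unadjusted is worth, under ANCOVA, 392 × (1 + r)/2 |
|---|---|---|
| 0.5 | 1.33 | 294 |
| 0.7 | 1.18 | 333 |
| 0.9 | 1.05 | 372 |

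**Peak troponin and CK-MB.** Assume lognormal data, a 15% lower peak (ratio 0.85), 392 per arm and two-sided alpha 0.05.
- Log scale: z = −ln(0.85) / (σ√(2/392)), with −ln(0.85) = 0.1625.
- Raw scale, control mean set to 1: z = 0.15 / √[(exp(σ²) − 1)(1 + 0.85²)/392].
- Power is Φ(z − 1.96).

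| assumed log-SD σ | raw z | raw power | log z | log power |
|---|---|---|---|---|
| 0.5 | 4.25 | 99% | 4.55 | 99% (99.5%) |
| 0.8 | 2.39 | 67% | 2.84 | 81% |
| 1.0 | 1.73 | 41% | 2.28 | 62% |

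At σ = 0.5 this effect is so large that both powers are near their ceiling. A fairer view sizes the effect for 80% power on the log scale at each σ and compares the t-test with the Wilcoxon test (2,000 simulated trials each):

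| assumed log-SD | t-test | Wilcoxon |
|---|---|---|
| 0.25 | 77% | 76% |
| 0.5 | 76% | 79% |
| 0.75 | 70% | 79% |
| 1.0 | 58% | 79% |
| 1.25 | 47% | 79% |

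The t-test's type I error was 4.5 to 5.5% throughout. If treatment instead only reduces the share of patients with prolonged or high values (22% against 14.1%, values multiplied by 1.5, 2 or 3), the order reverses: t-test 15%, 32% and 50%, Wilcoxon 12%, 27% and 39%.

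**AKI stages.** The Introduction puts 71% of cases in stage 1 and 12% in stage 3, which leaves 17% for stage 2. At a 22% placebo rate, 392 × 0.22 = 86.2 cases are expected, split 61.2 / 14.7 / 10.3. Suppose total AKI is unchanged and half of the 25.0 stage 2–3 cases become stage 1. Stage 1 then rises to 61.2 + 12.5 = 73.7, an apparent increase from a real improvement. In this scenario, and in one with a 36% cut:
- a Fisher comparison of stage 2 or higher has about 50% power (6.4% against 3.2%) and about 25% power (6.4% against 4.1%);
- an ordinal rank test over none/1/2/3 has only about 5 to 6%, which is no more than its type I error.

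**Stays.** This part needs no arithmetic. The two Table 3 definitions run to discharge, and neither says what ends the count for a patient who dies first.

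**The case against.** Several stronger readings are tempting, and the documents do not support them.

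- *The two sections contradict each other on the test.* They do not. The distribution rule under Statistical analyses concerns presentation, names no test, and may apply only to the baseline table. At most the sections differ on mean/SD against median/IQR.
- *The t-test is invalid for skewed data.* At 392 per arm it keeps its size, and mean days of stay is a legitimate target. The 30-day window also limits extreme stays.
- *Much of the power is wasted.* No SD is given. The loss is large only with heavy skew and a proportional effect.
- *The article fixes a separate Fisher test for each stage.* That is the natural reading, but it is inferred. A single Fisher test on the full table is not excluded.
- *An ordinal test would rescue the stage analysis.* If the relative risk of 0.64 held at every stage, separate Fisher tests would have 61%, 15% and 10% power, against 82% for an ordinal test. But the primary any-AKI test already has about 80%, so the ordinal test largely repeats it. As shown above, it does not detect a shift from stage 2–3 to stage 1. The low power for stages 2 and 3 comes mainly from few events.

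Other fair points stand. The unadjusted creatinine change is unbiased under randomisation. The creatinine course is a repeated measurement and so falls under the mixed models. All-cause mortality is collected separately and death is part of MAKE, so deaths are not hidden from the report. The analysis plan is not shown and may refine the methods. That does not remove the point, because the article states its t-test rule without condition.

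**Conclusion.** The point holds as an efficiency and interpretation issue in the secondary analyses.

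- The best-founded item is baseline adjustment of maximum creatinine change: a variance ratio of about 1.05 to 1.33, given equal variances and r between 0.9 and 0.5.
- Log-scale analysis of the biomarker peaks is a cheap gain of about 20 points at log-SD 1.0 and little up to 0.5. This is conditional on a lognormal shape and a proportional effect.
- The risk that a death passes for a short stay follows from the wording, but its size cannot be given because the article states no death rate.
- The stage 1 artefact is arithmetically possible under the article's own stage split. It calls for a comparison of stage 2 or higher.
- The inconsistency between the two sections is one of presentation only.

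Nothing here touches the primary analysis or the sample size.

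**What to change.** Before unblinding, replace the blanket t-test sentence with a method for each outcome:

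1. Maximum creatinine change: linear model adjusted for baseline creatinine (ANCOVA).
2. Peak troponin and CK-MB: analysis on the log scale, reported as ratios of geometric means with 95% CIs.
3. ICU and hospital stay: median and IQR, with a stated handling of deaths such that death cannot count as a short stay.
4. AKI severity: add a between-group comparison of stage 2 or higher and keep the single-stage counts descriptive.
5. Make the Statistical analyses and Secondary study outcomes sections agree on when mean/SD and when median/IQR is shown, and say whether the distribution rule reaches beyond the baseline table.

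The cost is wording and slightly more analysis work on the same data. A ratio of geometric means is less direct to read than a difference in means.
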